#### Experimental group

After randomization, 63 subjects will recive HJD Formula Granules and 63 subjects will recive HJD Elixation. The two groups will both take the drug by a single dose of 20 g, 3 times/day, before or after meals, coordinating with lifestyle interventions and continued for 12 weeks.

HJD Formula Granules are provided by Yifang Pharmaceutical Industry. Specifically, the single herb will first be decocted and concentrated to prepare the single herb granules, and then mixed different granules to form the formula granules of HJD. HJD Elixation is prepared by the Pharmacy Department of Shenzhen TCM Hospital. Specifically, the decoction pieces of various herbs are first mixed according to the dosage of HJD, and then form the granules after decocting, concentrating and drying. Whole ingredients of HJD Formula Granules and Elixation are as shown in the Table 2.

**Table 2 Tab2:** Whole ingredients of HJD Formula Granules and Elixation

Latin binomial nomenclature.	Chinese name	dosage
Rehmannia glutinosa Libosch.	Sheng Di Huang	30 g
*Ophiopogon japonicus* (L. f.) Ker-Gawl.	Mai Dong	20 g
Pseudostellaria heterophylla (Miq.)Pax ex Pax et Hoffm.	Tai Zi Shen	30 g
*Rheum officinale* Bail1.	Da Huang	6 g
Dioscorea opposita Thunb.	Shan Yao	10 g
Astragalus membranaceus (Fisch.) Bge.var.mongholicus (Bge.)Hsiao	Huang Qi	30 g
*Carthamus tinctorius* L.	Hong Hua	15 g
*Prunus persica*(L.)Batsch.	Tao Ren	10 g

#### Control group

The placebo control group (*n* = 63) will take the placebo by a single dose of 20 g, 3 times/day, before or after meals, coordinate with lifestyle interventions and continued for 12 weeks. The Chinese herbal medicine placebo contains pharmaceutical excipients, natural pigments, natural flavoring agents, and granules in the same amount as the test drugs. Its appearance, shape and taste are similar to HJD Formula Granules and HJD decoction Elixation, but it does not have efficacy.

### Outcome measurements

#### Sample collection, storage, analysis and destruction

Researches should communicate with subjects before sample collection, obtain consent of subjects, and sign informed consent. Subjects are forbidden to eat, drink, brush and floss teeth 12 hours before sample collection.Blood collection: 5 ml blood sample should be collected from the median cubital vein at 8:00 a.m. when participants are fasting for more than 8 hours.Saliva collection: Samples will be collected at 8:00 a.m. when participants are fasting for more than 8 hours. Non-irritating methods will be employed to collect saliva samples which should flow naturally into 50 ml EP tube instead of expectorating until 10 ml saliva is collected.Supringival plaque samples collection: Researcher should use sterile curettles to scrape the plaque of subjects’ upper and lower anterior teeth, premolars and buccal side of molars, and place the supringival plaque samples in 1.5 mL EP tubes.Intestinal flora collection: Researcher should collect 2-5 g of fresh and naturally discharged stool samples (the middle part of the stool) with fecal DNA collection tube, avoid mixing with urine or other substances, and replace the clean 5 ml centrifuge tube cover and tighten the collection tube again.

Samples should be placed in − 80 °C refrigerator immediately after collection, and avoid repeated freezing and thawing.

After each sample is analyzed, it will undergo harmless treatment according to the requirements of laboratory waste.

#### Observation index and laboratory examination

During the visit, investigators will arrange the subjects to complete the corresponding examination according to the study progress. Except for physical examination, electrocardiogram and other routine examination, the 3-alternative forced-choice procedure (3-AFC) [32] will be used to detect the threshold of linoleic acid (LA). Subjects in each group will be also guided to complete a modified questionnaire [33] to determine their dietary preferences during the previous 3 months. Saliva and stool samples collected during the study will be analyzed for metabonomics. Specific methods are as follows:Complete physical examination: Specific examination items include general condition (height, weight, BMI, and abdominal circumference), respiratory, cardiovascular, abdominal, skin, head and neck, lymph nodes, thyroid, musculoskeletal (including spine and limbs) and nervous system examination.Routine biochemical tests: Specific tests include blood routine, urine routine, routine stool test, fasting blood glucose (FBG), 2-hour postprandial blood glucose (2hPG), fasting C-peptide, 2-hour postprandial C-peptide, fasting insulin, 2-hour postprandial insulin, hemoglobin A1c (HbA1c), liver function, renal function, and blood lipid. The above tests will be completed by the medical laboratory of Shenzhen TCM Hospital.Oral LA threshold determination: The threshold will be tested by 3-AFC. The solutions used in the test take deionized water as solute, then add 5% edible grade acacia gum and antioxidant 0.01% EDTA, mix thoroughly with blender for 2 minutes, add 5% edible grade liquid paraffin, mix well again, add edible grade LA, and prepare concentration gradients of 0.02, 0.06, 1,1.4, 2, 2.8, 3.8, 5, 6.4, 8,9.8, 12,20 mmol/L LA solution respectively. Blank control solution does not contain LA. All solutions are prepared on the same day and then stored at 4 °C for later use. Subjects should fast for at least 8 hours before testing.

During the test, the room should be lit red to avoid visual interference, and the subjects ware nose clips to avoid olfactory interference. At the beginning, each concentration of LA is divided into groups, and each group is lined with 3 small containers, one of which contains different concentrations of LA solution, and the other two are blank control solutions. Starting with the lowest concentration group, subjects are asked to attempt the solutions to identify the LA solution in each of the three containers. At the end of each attempt, they should spit out the solution at the end of each attempt and gargle with deionized water. If the subject is identified incorrectly, he/she will be asked to try the next group with a higher concentration of LA solution. If the subject is identified correctly, the test will be repeated another two times with the same concentration of LA solution. If the subject successfully identifies the same concentration of the solution three times consecutively, this concentration will be the subject’s oral LA-threshold (As shown in Fig. 2).

**Fig. 2 Fig2:**
[figure not shown]
Schematic diagram of 3-alternative forced-choice procedure for detection of oral linoleic acid threshold

(4).Dietary preference assessment: Dietary preferences will be evaluated by the questionnaire of dietary status in the last 3 months. (As shown in Table 3).

**Table 3 Tab3:** Modified dietary preference questionnaires

1. What do you think of your daily food intake? (A) overeating (B) just enough (C) not enough 2. Won’t you feel full until you eat enough? (A) often (B) occasionally (C) feeling full soon before eating enough 3. Do you like rich food? (A) very (B) average (C) not very much (D) very not 4. How often do you eat sweets? (A) often (B) sometimes (C) not often (D) not at all 5. What’s your taste preference? (A) sweet (B) sour (C) bitter (D) spicy (E) salty (F) others 6. What are your diet preference? (A) oily food (B) salty food (C) spicy food (D) light food 7. Which cooking oil do you use most often? (A) vegetable oil (peanut oil, soybean oil, blend oil, or rapeseed oil, etc.) (B) animal oil (lard or butter, etc.) 8. Please recall whether you have eaten any of the following foods in the past 3 months and estimate the average frequency of the intake of these foods. Tick the box that matches your actual intake situation							
Time	≥3 times a day	1–2 times a day	5–6 times a week	3–4 times a week	1–2 times a week	1–3 times a month	≤1 times a month
Type							
Animal skin (fat or offal)							
Cream products (chocolate, cake, bread, or ice cream, etc.)							
Nuts (peanuts, walnuts, or sesame, etc.)							
Fried food (fried dough sticks, French fries, buns, or barbecue, etc.)							
Processed meat (canned meat, ham sausage, or bacon, etc.)							

(5).Saliva and intestinal microbiota testing: After thaweding saliva and stool samples, total DNA is extracted using commercial bacterial community DNA extraction kit. After the DNA quality inspection, PCR amplification, product purification and PCR product quantification, 16-second high-throughput sequencing is performed using HiSeq 2500. Bioinformatics analysis is then conducted: After quality assurance of the raw data, the data are de-chimerized and clustered using USearch software. Reads are first sorted according to their abundance from large to small, and obtain OUT (Perational Taxonomic Units) by standard clustering with 97% similarity. Each OUT is thought to represent a species. Following that, Reads from each specimen are extracted at random, and the correlating OUT sequence is extracted. Then, using Qiime software to draw the alpha diversity index dilution curve, and select sensible extraction parameters based on the dilution curve. Use Qiime software to analyze the OUT obtained after extraction. First, a Read is extracted from OUT as a representative sequence. Each OUT will be classified by RDP method to compare the representative sequence with 16S database. After classification, the OUT abundance table is generated based on the number of sequences in each OUT, and the successive analysis is conducted on the basis of the table.(6).Saliva and intestinal metabolite group detection: After thawing, the saliva and stool samples are mixed, centrifuged, mixed with water of DSS internal standard, centrifuged at low temperature and high speed and detected in a nuclear magnetic tube. 1H-NMR free induction decay (FID) signal will be imported into Chenomx NMR suit (Version 8.0, Chenomx, Edmonton, Canada), and then act Fourier transform, phase adjustment, and baseline correction automatically. Dss-d6 peak (0.0 PPM) is adopted as the chemical shift standard for the whole spectrum, and the spectrum peak shape (CSI) is adjusted by inverse convolution operation. The concentration and peak area of DSS-D6 are used as standards based on signal information in the 1H-NMR spectrum (such as chemical shift, peak shape, half-peak width, and coupling splitting score), and the signal of sample spectrum is compared and analyzed one by one in combination with Chenomx’s own database to obtain the metabolites and the corresponding absolute concentration value. Metabolomics data will be processed using R language, and perform principal component analysis (PCA) and partial least square analysis (PLS-DA) followed by metabolic pathway analysis.(7).Electrocardiogram examination: Electrocardiogram (ECG) is required during the stage of screening. After the subject has rested for at least 5 minutes, the 12-lead ECG should be performed and recorded on the CRFs as “normal” or “abnormal”.

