**Methods:**

This is a prospective, randomized, double-blind, and placebo-controlled clinical trial. A total of 183 participants are randomly assigned to HJD Formula Granules plus lifestyle intervention, HJD Elixation plus lifestyle intervention, and placebo plus lifestyle intervention. All subjects undergo 1 day of screening before participating in the study, followed by 84 days of drug intervention and observation. During and after treatment, the main outcome measures include fasting blood glucose and 2-hour postprandial blood glucose.

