**Fig. 1 Fig1:**
[figure not shown]
Study flowchart. Members with prediabetes will be enrolled and allocated randomly to one of three groups. All subjects will accept 1 day of screening, and 84 days of intervention and observation. The data is gathered to verify the clinical effectiveness and possible mechanism of Huoxue-Jangtang Decoction (HJD) in the treatment of prediabetes, and to prove the consistency of HJD Formula Granules with HJD Elixation

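### The two lowest frequency boxes in item 8 of the dietary questionnaire (Table 3) overlap at once a month; the 3-month recall at day 84 is a smaller wording point

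*Protocol article*

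**What the plan says.** The section on secondary outcomes lists dietary preference, and the Discussion makes it a goal to learn whether the formula shifts preference for fat.

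Under the heading on observation index and laboratory examination, participants are to "complete a modified questionnaire [33] to determine their dietary preferences during the previous 3 months". Item (4) of the same list repeats the period: "Dietary preferences will be evaluated by the questionnaire of dietary status in the last 3 months".

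Table 3 prints the form. Items 1 to 7 ask about present habits and likes and carry no recall period of their own. Item 8 does: "Please recall whether you have eaten any of the following foods in the past 3 months and estimate the average frequency". It covers five food types, each with seven frequency boxes, of which the last is "≤1 times a month" and the one before it covers one to three times monthly.

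On duration, the abstract has screening "followed by 84 days of drug intervention and observation", the Fig. 1 caption says "All subjects will accept 1 day of screening, and 84 days of intervention and observation", and the section on the experimental group has dosing "coordinating with lifestyle interventions and continued for 12 weeks". Twelve weeks are 84 days, so these agree.

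**The concern.** Response categories for a frequency question should be mutually exclusive. Where two boxes share a value, the answer depends on which box the participant happens to choose, and that choice need not be the same at two assessments or in two people with equal intake. The result is apparent change, or an apparent difference, with no difference in diet behind it. Item 8 is the only part of the form that records how often named, mostly fat-rich foods are eaten, so it is the part most likely to be used for the fat-preference question.

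The recall period raises a separate and smaller question. Three calendar months are slightly longer than 84 days, so a form completed at day 84 takes in a few days before the first dose and averages over the whole of treatment. If the intended target is intake at the end of treatment, such an average can fall short of it.

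**Working it through.** The article states no sample size, effect or score for this outcome, so there is no figure of the plan to reproduce.

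**Boxes.** Inputs: the seven box labels in Table 3.

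1. In descending order they cover: at least 3 a day; 1 to 2 a day; 5 to 6 a week; 3 to 4 a week; 1 to 2 a week; 1 to 3 a month; at most 1 a month.
2. Comparing neighbours in whole counts, the first five boxes share no value, and the lower end of the fifth (once a week, more than 3 a month) lies above the top of the sixth.
3. The sixth and seventh share the value 1 a month. As occasions in three months, the sixth covers 3 to 9 (3 × 1 to 3 × 3) and the seventh 0 to 3 (3 × 0 to 3 × 1). They meet at 3.
4. A participant who eats a food once a month at both of two assessments has 2 × 2 = 4 admissible answer pairs. Two of them (sixth then seventh, seventh then sixth) show a move of one category although intake is constant.

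**Recall period.** Inputs: treatment T = 84 days (abstract; experimental group section); recall window W = 3 months (Table 3, item 8). The article gives no day count for three months, so W = 89 to 92 is assumed. Completion at day 84 is also assumed, because the schedule in Table 1 is not shown.

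1. Days before the first dose = W − T: 89 − 84 = 5; 92 − 84 = 8.
2. Share of the window = (W − T)/W: 5/89 = 5.6%; 8/92 = 8.7%. If three months are read as 12 weeks, it is 0%.
3. Share of the end-of-treatment effect seen in the average, if the effect is complete from day 0, = T/W: 84/92 = 91% to 84/89 = 94%.
4. If instead the effect rises linearly to full size at day m and then holds, the share is (84 − m/2)/W. The values of m below are assumptions for illustration.

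| m (assumed) | (84 − m/2)/W | Share seen |
|---|---|---|
| 0 | 84/92 to 84/89 | 91% to 94% |
| 28 | 70/92 to 70/89 | 76% to 79% |
| 56 | 56/92 to 56/89 | 61% to 63% |
| 84 | 42/92 to 42/89 | 46% to 47% |

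The pre-dose days alone cost at most 9% of the effect. Everything beyond that comes from the assumed build-up.

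**The case against.** Against the box point: it concerns one value, between the two lowest categories, on one item of a secondary outcome. Treatment is blinded, so there is no reason for the choice of box to differ by arm. The article does not say how item 8 is scored, and a score that treats the two lowest boxes alike would make the overlap harmless. All of this stands and limits the point to a minor one. It does not make the printed categories exclusive.

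Against the recall point: at day 84 the window and the treatment period almost coincide, and average intake on treatment is a legitimate measure. That also stands.

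Three stronger readings are tempting, and the article does not support them.

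- *That the 3-month recall dilutes any effect, perhaps by half.* The low shares in the table follow from a slow onset, and the article gives no onset time for a dietary effect. With immediate onset, more than 90% is seen. The averaging also applies only to item 8 as worded; items 1 to 7 are in the present tense, although the text labels the whole form as covering three months.
- *That the form mostly measures pre-treatment diet at earlier visits.* No visible text says it is used then. The 28-day figure in the Intervention section is a drug supply, and the visit schedule is not shown.
- *That the item should move to a 4-week recall.* That changes the target rather than correcting an error. Recruitment began on June 1, 2022, so participants already enrolled may have 3-month baselines, and two instruments would be mixed within or between participants.

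Nor does dilution follow from the overlapping boxes: they misclassify between neighbours and have nothing to do with averaging over time.

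**Conclusion.** The point holds as a minor one. The overlap at once a month is certain from the printed form and depends on no assumption. Its effect is noise of one category for foods eaten about once a month. How many answers that concerns cannot be judged from the article. The false change between assessments presumes that the form is completed more than once, which the goal of detecting a shift in preference implies; with a single completion, the same noise would appear between participants.

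The recall mismatch is real but slight: 5 to 8 pre-dose days, 5.6% to 8.7% of the window, assuming completion at day 84 and 89 to 92 days for three months. The item measures average intake over treatment and understates the end-of-treatment effect only as far as the effect builds up gradually, by an amount the article gives no means to fix. No primary outcome is affected.

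**What to change.** 1. Relabel the last box of item 8 *less than once a month or never*. Every frequency then fits one box, and once a month belongs to the sixth. This costs a reprint of one form.
2. Leave answers on forms already completed as they are. As a sensitivity check, repeat the item 8 analysis with the two lowest boxes merged into a single category of at most three times a month. Old and new forms are then on the same scale. The cost is that the merged analysis cannot separate rare from occasional intake, which is why it is a check and not the main analysis.
3. As an optional improvement, word item 8 at day 84 as intake *since starting the study treatment* and leave the baseline item unchanged. This removes the pre-dose days. The windows then differ in length by 5 to 8 days, which matters little because the item asks for an average rate. Record which wording each participant received. Stating that the item is meant to capture average intake on treatment would settle the question of target.

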
#### Primary outcomes

The primary outcome is to verify the clinical efficacy and possible mechanism of HJD in the treatment of prediabetes, and to prove the consistency of HJD Formula Granules with HJD Elixation.

It specifically includes the change value of HBA1c, FBG, 2hPG prior to and following treatment.

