## Abstract

**Background:**

Prediabetes is a hypermetabolic syndrome with blood sugar levels falling between the normal and diabetes. People with prediabetes have a significantly increased chances of developing diabetes, cardiovascular and cerebrovascular diseases, tumors, dementia, and other diseases in the future when compared to the healthy population. However, prediabetes is mainly treated based on lifestyle intervention, currently without targeted drug treatment plan. Traditional Chinese medicine (TCM), which has a longstanding experience, has been shown in clinical studies to be effective for the treatment of diabetes and its related complications. Furthermore, different dosage forms such as decoction and granule have developed gradually in clinical application. Preliminary studies have found that Huoxue-Jangtang Decoction (HJD), with good hypoglycemic and lipid-regulating effects, is potentially one of the complementary and alternative treatments for prediabetes. Therefore, this project intends to perform a prospective clinical study to observe the clinical effectiveness of HJD on prediabetes and the consistency of the efficacy of formula granules and the elixation.

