### Participants

#### Sample size

Sample size is calculated by PASS 15.0 software, with the significance level of 0.05. A total of 189 cases (63 cases in each group) are required to detect inter-group differences in 2.6 mmol/L postprandial 2 h glucose, with a statistical power of 90%. The sample size calculation assumes a standard deviation of 2.0 mmol/L and a shedding rate of 20%.

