### Statistical analysis

Primary, secondary, exploratory end points and safety assessments will be analyzed when the last patient completes the follow-up or drops out of the study. Analyses of clinical data will be performed by the principal investigator including subjects’ demographic, clinical, and laboratory data.

Continuous variables are used to evaluate the number of cases, mean, standard deviation, median, minimum, and maximum for demographic data and other baseline eigenvalues. Frequency and composition ratio are calculated using count and grade data. Descriptive results invole inferential statistical results (*p*-values).

For the analyses of laboratory data and clinical efficacy of drugs, chi-square test or Fisher’s exact test are used for counting data, while ANOVA and T test are used for measurement data. The grade data is analyzed by Ridit and CMH. The ratio or percentage of counting data is expressed, and the measurement data is expressed as mean ± standard deviation. All statistical tests are conducted by two-sided tests, with *P* < 0.05 indicating statistical significance. Multiple imputation will be used for missing data.

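### Consistency of the two HJD preparations is a primary claim, but it does not depend on either beating placebo and rests only on difference tests

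*Protocol article*

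**What the plan says.** The Primary outcomes section joins two claims, to "verify the clinical efficacy and possible mechanism of HJD in the treatment of prediabetes, and to prove the consistency" of the two preparations, and measures both by the change in HbA1c, fasting glucose and 2-hour glucose. The abstract gives the same pair of aims: "observe the clinical effectiveness of HJD on prediabetes and the consistency of the efficacy of formula granules and the elixation". The Background section makes clear that agreement in efficacy is meant, because it describes evidence of that agreement as lacking.

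The Statistical analysis section covers continuous data in one clause, "while ANOVA and T test are used for measurement data", and adds "All statistical tests are conducted by two-sided tests" with P < 0.05 as the criterion. It does not say which groups each test compares. It names no equivalence or non-inferiority test and no margin. No section makes the consistency conclusion conditional on a result against placebo, although the Randomization section allocates 63 patients to placebo.

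**The concern.** Two products can agree in efficacy only if they have some. A comparison of Formula Granules with Elixation looks only at the difference between them, so it gives the same answer whether both work equally well or neither works. The placebo arm tells these cases apart, but the plan does not tie the consistency claim to it.

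The only tests named are tests for a difference. If a non-significant result were taken as proof of consistency, the claim would usually succeed whenever the two products are alike, including when both are inert. The inert case is not remote for every primary variable: the Discussion cites an earlier multi-centre trial of TCM granules in prediabetes that found no improvement in HbA1c, which is one of the three primary variables here. At stake is a published statement that the granules may replace the decoction, on evidence that would look the same for two inactive preparations.

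**Working it through.** **Inputs.** From the Sample size section: "with the significance level of 0.05"; "with a statistical power of 90" per cent; "required to detect inter-group differences in 2.6 mmol/L postprandial 2 h glucose"; and "The sample size calculation assumes a standard deviation of 2.0 mmol/L and a shedding rate of 20" per cent. The planned size is 63 per group, so evaluable patients per group are 63 × 0.8 = 50.4, taken as 50. Margins of 1.0 and 1.3 mmol/L and effects below 2.6 mmol/L are assumptions, because the article gives none.

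**The plan's own figure.** n per group = 2 × (1.960 + 1.282)² × 2.0² / 2.6² = 12.4, so 13, or 17 after dropout and 51 in total. The stated 63 per group (189) is not reproduced. A difference of 1.3 mmol/L gives 49.7, so 50, and 50 / 0.8 = 62.5, so 63. That mismatch is a separate matter. It is noted here because the calculation is for detecting a difference and has no equivalence component.

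**Step 1: difference test between the products.** If the true difference is zero, a two-sided 5% test is non-significant 95% of the time by construction. A simulation of three arms with 50 each and SD 2.0 confirms that this does not depend on efficacy:

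| Common effect of both products vs placebo | Granules vs Elixation non-significant |
|---|---|
| 0 (both inert) | 94.8% |
| 0.8 mmol/L | 95.0% |
| 2.6 mmol/L | 94.9% |

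With both inert, about 88% of trials show no significant difference in any of the three pairs.

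**Step 2: would an equivalence test alone repair this?** SE of the difference = 2.0 × √(2/50) = 0.400. With a true difference of zero, the chance of passing is 2Φ(margin/SE − z) − 1.

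- Margin 1.0, one-sided 0.05: 2Φ(2.50 − 1.645) − 1 = 61%.
- Margin 1.3, one-sided 0.05: 2Φ(3.25 − 1.645) − 1 = 89%.
- At one-sided 0.025 (z = 1.960): 41% and 80%.

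The common effect against placebo does not appear in the formula, so two inert products pass as often as two equally active ones.

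**Step 3: what an efficacy condition does.** If both products are inert, both differ significantly from placebo in about 0.8% of simulated trials, counting either direction. A false claim of consistency therefore becomes rare on any one variable. If both products share a true effect, the condition is met as follows (50 per arm, SD 2.0, two-sided 0.05):

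| Common effect (mmol/L) | One given product beats placebo | Both beat placebo |
|---|---|---|
| 0.8 | 51% | about 34% |
| 1.0 | 70% | about 55% |
| 1.3 | 90% | about 83% |
| 2.6 (protocol) | about 100% | about 100% |

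**The case against.** The strongest reply is that this is a journal article. Which groups each test compares, in what order and against what margin could all be set in an analysis plan that is not shown. The article also names efficacy and consistency together as the primary aim and speaks of consistency of efficacy, so a failure against placebo would be visible in the same report. Much of this stands. The article does not say that a non-significant difference will be read as consistency, and the absence of a margin would not be a finding by itself. What does not fall away is that the article states its primary claims and the kind of test behind them. Those tests look for differences, and nothing bars the consistency claim when efficacy fails.

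A reader might infer more: that the plan prescribes a three-group ANOVA followed by separate t tests, and that power is lost because the two HJD arms are not pooled against placebo. The documents do not support this. The Statistical analysis section assigns no test to any pair of groups. At the protocol's own 2.6 mmol/L and SD 2.0, the F test, the pairwise t test and a pooled contrast all have about 100% power, so the two placebo comparisons would not disagree either. Pooling gains power only at smaller assumed effects (63 / 82 / 96% against 51 / 70 / 90% pairwise at 0.8 / 1.0 / 1.3 mmol/L). It costs power if only one product works: about 47% against 90% at 1.3. The Experimental group section describes two different manufacturing routes, so testing each product against placebo is a legitimate choice.

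**Conclusion.** The point holds in this form: a primary claim of consistency is made without requiring efficacy, and the named analysis tests only for difference. Two inactive products would appear not to differ about 95% of the time. They would also pass an equivalence test in 61% to 89% of trials at margins of 1.0 to 1.3 mmol/L (one-sided 0.05), or 41% to 80% at one-sided 0.025. The 95% figure needs only a true difference of zero and a 5% test. The equivalence figures rest on the assumed margins, 50 evaluable per arm and the protocol's SD of 2.0 for 2-hour glucose. No corresponding figures can be given for HbA1c or fasting glucose, since the article states no SD for them. The finding does not extend to a loss of power or to a need for a pooled HJD contrast.

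**What to change.** State in the protocol, and carry into the analysis plan, that for each primary variable:

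1. Consistency is claimed only if Formula Granules and Elixation have each been shown better than placebo on that variable.
2. The claim then rests on the confidence interval for Formula Granules minus Elixation lying within a margin stated and justified in advance, with its confidence level named. A non-significant difference is not evidence of consistency.
3. All three pairwise differences are reported with 95% confidence intervals. HJD combined against placebo may be added as a supporting estimate.

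The condition should apply to each product rather than to the combined arms. With one product at an assumed 0.8 mmol/L and the other inert (50 per arm), a pooled condition would be met in 21% of trials, and in 48% of those the two products would not differ significantly.

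The change needs no new patients, visits or measurements. The cost is that consistency can be claimed less often: the condition is met in about 34 / 55 / 83% of trials at assumed effects of 0.8 / 1.0 / 1.3 mmol/L. At the printed 2.6 mmol/L it is met almost always. The interval must then still fall within the chosen margin.
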